## Abstract

**Background:**

About 1 in 3 individuals will sustain a secondary anterior cruciate ligament (ACL) injury within 24 months of returning to sport after ACL reconstruction (ACLR). While aberrant biomechanics and poor quadriceps strength have been associated with secondary ACL injury risk, unresolved injury-related fear has also been identified as a potential risk factor for additional ACL injuries in previously high-functioning, physically active populations. Virtual reality mindfulness meditation (VRMM) is a psychological intervention that may reduce injury-related fear and improve an individual’s ability to stay in the present moment during stressful situations such as sport. There is a critical need to identify whether VRMM is a feasible intervention that could be implemented to address injury-related fear and reduce secondary ACL injury risk.

**Objective:**

This study aims to determine the feasibility, acceptability, and preliminary efficacy of a VRMM intervention with neuromuscular training rehabilitation (NTR) to reduce injury-related fear and improve jump-landing biomechanics in females with a history of ACLR, when compared to a sham virtual reality (VR) intervention+NTR.

**Methods:**

A double-blinded, 2-arm feasibility trial of 48 participants (24 per group) comparing VRMM+NTR and VR sham+NTR will be conducted. Recruitment, retention, adherence, and acceptability outcomes will be collected throughout the trial. Injury-related fear will be measured using the 11-Item Tampa Scale of Kinesiophobia. Jump-landing biomechanics will be assessed via peak knee abduction moment and peak knee flexion excursion. The change in outcomes will be compared between groups using 2×2 repeated measures ANOVA and partial η^2^ effect sizes. Significance will be set at *P*<.05.

**Results:**

The study was funded in May 2021. The trial started in September 2023 and is anticipated to be completed in May 2027, with the first results expected to be submitted for publication in winter 2027. We expect to observe acceptable rates of retention, adherence, and acceptability to the VRMM intervention and more favorable outcomes in the VRMM+NTR group compared to the VR sham+NTR group. As of now, 55 participants have been screened for eligibility, of which 33 were ineligible. Twelve participants have been randomized, and 10 have completed the trial. Two participants withdrew from the trial before the completion of the full intervention protocol due to the study time commitment.

**Conclusions:**

The results of this trial will improve our understanding of the feasibility of VRMM and inform the next steps in behavioral intervention development to test the efficacy of VRMM in reducing injury-related fear in females after ACLR.

## Introduction

Anterior cruciate ligament (ACL) injury is a traumatic knee injury that results in decreased quality of life, time loss from sport, and persistent knee symptoms, often leading to ACL reconstruction (ACLR) to restore knee stability [1]. ACLR helps patients return to previous levels of sports participation and engage in lifelong physical activity [1]. However, 1 out of 3 patients post-ACLR will not return to previous levels of sport participation, and injury-related fear is one of the primary barriers associated with failure to return to sport and decreased physical activity after ACLR [2-4]. Additionally, individuals with a history of ACLR who exhibit increased levels of injury-related fear also exhibit aberrant walking and jump-landing biomechanics after ACLR [5-7], with changes in jump-landing biomechanics being strongly associated with secondary ACL injury risk [8]. Supporting these associations, Paterno et al [9] identified that patients with increased injury-related fear after ACLR who return to sport are 13 times more likely to sustain a secondary ACL injury within 24 months when compared to those with lower levels of injury-related fear [9]. However, current rehabilitation programs often emphasize improvements in structural or biological aspects of the injury (eg, graft healing, neuromuscular training to address strength deficits, and improvement in range of motion) [10] and fail to address the psychological consequences of ACL injury and ACLR. As injury-related fear is associated with aberrant biomechanics and secondary ACL injury risk, there is a critical need to address injury-related fear to improve pertinent clinical outcomes after ACLR.

The stress and injury model is a theoretical model that may help to explain the relationship between injury-related fear and secondary ACL injury risk post-ACLR. This model hypothesizes that personality factors, history of stressors (eg, ACL injury), and coping strategies influence an individuals’ stress response (ie, cognitive appraisals, attentional demands, and physiological changes) and subsequent injury risk in an athletic context [11,12]. The stress and injury model proposes that encountering a stressful sports-specific situation (eg, a situation that mirrors the experience or mechanism of an individual’s ACL injury) may negatively affect an individual’s attentional control and lead to processing of irrelevant information [11,12]. During a heightened stress response, individuals may be unable to stay in the present and effectively attend to the situation, which may increase their risk to sustain a secondary ACL injury [13]. Attentional changes associated with injury-related fear may affect signaling from the central to the peripheral nervous system during sport-specific tasks, leading to cognitive-motor interference and altered knee joint biomechanics. For example, it has been observed that patients after ACLR exhibit changes in brain activity associated with attentional and emotional processing, including overactivity in the default mode network brain regions in females post ACLR [14-17]. Therefore, the cycle of ACL injury and secondary injuries may be perpetuated by increased injury-related fear, overactivity in emotional regulation, an inability to modulate attentional controls in brain regions (ie, default mode network), and altered jump-landing biomechanics (Figure 1).

**Figure 1. F1:**
[figure not shown]
Hypothesized cycle of ACL injury, injury-related fear, and secondary ACL injury. ACL: anterior cruciate ligament; ACLR: anterior cruciate ligament reconstruction.

The stress and injury model also proposes that interventions can be used to modify the stress response to reduce its impact when an athlete is faced with a stressful athletic situation. One intervention that may be helpful in addressing both emotion regulation and attentional control is mindfulness [18]. Mindfulness is a state of awareness of the present moment and allows for self-regulation of emotions and attention by decreasing rumination about past or future events [19]. Mindfulness can be cultivated through structural practices, such as mindfulness meditation, which encourages redirecting attention to a focal cue (eg, breath) to stay in the present moment [19]. During the practice of mindfulness, the individual is aware of all incoming thoughts and feelings, but rather than reacting to them, the individual accepts them and then continues to focus on the present moment, whether that is focusing on their breathing, movement, bodily sensations, or thoughts [19].

A positive association between mindfulness and psychological health and well-being has been identified [20-22]. Mindfulness interventions have led to the modulation of brain regions involved in emotional regulation and to improved attentional control in chronic pain and psychopathological populations [14-17], as well as reduced anxiety and fear in injured athletes, including patients with patellofemoral pain [23,24]. However, the effectiveness of mindfulness in improving functional outcomes, such as jump-landing biomechanics, has not been investigated in patients after ACLR. Improved emotional regulation and attentional control in sporting situations could improve biomechanics and decrease secondary ACL injury risk. Therefore, there is a critical need to explore whether mindfulness can improve clinically relevant outcomes in patients after ACLR.

Using established frameworks, such as the National Institutes of Health (NIH) stage model, can enhance our ability to generate and test interventions that can be implemented in real-world settings to address injury-related fear after ACLR. The NIH stage model consists of 6 different stages: basic science (stage 0); intervention generation, modification, refinement, adaptation, pilot, and feasibility testing (stage 1); traditional efficacy testing (stage 2); efficacy testing with real-world providers (stage 3); effectiveness research (stage 4); and dissemination and implementation research (stage 5) [25]. Stage 1 consists of all activities needed to create, test, and enhance the rigor of the behavioral intervention, including identifying implementation barriers from patients and providers. For example, it has been established that sports medicine providers are able to identify injury-related fear after a sport-related injury, but also report decreased confidence in implementing psychological skills and a lack of time for engaging in these approaches to address injury-related fear as common barriers [26]. Therefore, proposed interventions should consider solutions that will address these barriers to enhance the likelihood of implementation in real-world clinical settings.

Using technology-driven strategies may help reduce the associated implementation barriers for sports medicine providers in adopting psychologically informed approaches, such as mindfulness. The use of virtual reality (VR) can help to address these barriers by providing a plug-and-play solution while also enhancing the efficacy of mindfulness delivered to patients after ACLR. Furthermore, for novice meditators, VR can enhance the efficacy of mindfulness by engaging auditory and visual senses as attentional anchors to enhance the mindfulness experience [27-30]. Given the positive influence of VR mindfulness practices on outcomes in other clinical populations [27-30], and the opportunity to reduce known barriers to engaging in psychologically informed approaches in sport-related injury rehabilitation, there is a critical need to explore the efficacy of VR mindfulness practices in patients after ACLR. Furthermore, it is important to explore this intervention in a patient population most at risk for sustaining primary ACL injuries [31] and less likely to return to preinjury sport after ACLR [32] (ie, female athletes).

Female athletes are known to have higher sport dropout rates in adolescence, be at a greater risk of primary ACL injury, and may return to sport at lower rates following ACL injury for a multitude of reasons [31]. Additionally, female athletes post ACLR report differences in types of injury-related fear when compared to their male counterparts [33]. Consequently, when developing the proposed trial, we opted to recruit only female athletes post ACLR, as a fully powered study able to identify these nuances in sex differences would require substantially more resources than available. Therefore, the purpose of this study is to determine the feasibility (aim 1) and preliminary efficacy of an 8-week virtual reality mindfulness meditation (VRMM) intervention to decrease self-reported injury-related fear (aim 2a) and improve jump-landing biomechanics (aim 2b) in females cleared to return to activity post ACLR. We hypothesize that females cleared to return to activity post ACLR who undergo VRMM will demonstrate improvements in these surrogate end points associated with secondary ACL injury risk.

## Methods

### Study Design

A double-blinded, 2-arm feasibility trial will be conducted to investigate a VRMM intervention. To address aim 1, recruitment, retention, adherence, and acceptability outcomes will be collected throughout the trial. To address aim 2, changes in injury-related fear and jump-landing biomechanics will be compared between participants randomized to VRMM+neuromuscular training rehabilitation (NTR) or VR sham+NTR. The study schedule is outlined in Table 1.

**Table 1. T1:** Schedule of events for the trial.

	Screening	Preassessment (wk 1)	Week 1 (3 visits)	Week 2 (3 visits)	Week 3 (3 visits)	Week 4 (3 visits)	Week 5 (3 visits)	Week 6 (3 visits)	Week 7 (3 visits)	Week 8 (3 visits)	Postassessment (wk 8)
Review eligibility	✓										
Informed consent		✓									
Demographics		✓									✓
Clinical history		✓									
Height and weight		✓									✓
Knee-related questionnaires IKDC^a^ Tegner ACL-RSI^b^		✓									✓
Injury-related fear (TSK-11)^c^	✓	✓									✓
Jump-landing biomechanics (LESS-RT)^d^	✓										
Jump-landing biomechanics (motion capture)		✓									✓
Adherence log			✓	✓	✓	✓	✓	✓	✓	✓	
Acceptability survey											✓
Randomization		✓									
Control and experimental intervention (neuromuscular training and virtual reality)			✓	✓	✓	✓	✓	✓	✓	✓	
Adverse event reporting		✓	✓	✓	✓	✓	✓	✓	✓	✓	✓

a IKDC: International Knee Documentation Committee.

b ACL-RSI: anterior cruciate ligament–return to sport after injury scale.

c TSK-11: 11-Item Tampa Scale of Kinesiophobia.

d LESS-RT: Landing Error Scoring System-Real Time.

### Sample Size Estimation and Study Population

For early-stage pilot and feasibility studies, it has been suggested to include at least 12 participants per group [34]. To achieve aim 1, a minimum of 12 participants in each group will be enrolled (ie, 24 participants). However, we also completed an *a priori power* calculation that determined a sample size of 20 participants per group (40 participants in total), which was required to achieve 80% power to detect a large between-group effect in injury-related fear. This calculation was based on a repeated measures ANOVA with a common SD of 1, a 2-sided α level of 0.05, and an estimated partial η^2^ of 0.23 [35] (moderate effect size) between the intervention and sham groups in injury-related fear. Therefore, a total of 48 participants (24 in each group) will be recruited to account for a 20% dropout rate in the sample and will be appropriate for making interpretations for aims 1 and 2.

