### Outcomes

#### Feasibility (Aim 1)

Recruitment and retention (ie, screening, enrollment, consent, randomization, intervention/sham completion, and study completion) will be documented throughout the trial (Figure 2). Monthly recruitment rates will be calculated as the number of recruited and consented participants divided by the number of eligible participants (ie, those screened into the study). Regular enrollment reports outlining this information are being sent to the federal agency monthly. The goal recruitment rate is 1 to 3 participants per month over a 45-month timeframe (September 2023 to May 2027). Retention will be calculated as the percentage of participants retained during the 8-week period, and all reasons for dropout will be documented. We expect that more than 75% of participants will be retained during the 8-week period for both VRMM+NTR and VR sham+NTR groups.

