### Limitations and Anticipated Problems

This trial is designed to assess the feasibility and preliminary efficacy of VRMM in patients after ACLR. Therefore, we will not be able to draw any firm conclusions regarding the effectiveness of the VRMM intervention to improve the measured outcomes in this population. A larger randomized clinical trial will be needed to investigate the efficacy of VRMM+NTR compared to VR sham+NTR. The results from this trial will determine whether such a study is feasible and how a fully powered clinical trial may be optimally designed for this purpose.

Additionally, there are a total of 26 participant visits from preassessment to postassessment involved in this trial. Therefore, it is possible that participants may drop out, miss a study visit/visits, or that there may be missing data, which would introduce a risk of attrition bias. The feasibility outcomes are being used to understand these factors, and our sample size was calculated to account for possible attrition. Finally, the TSK-11 scale will be interpreted cautiously in view of the limitation that the scale was not developed specifically for acute musculoskeletal injuries; however, psychometric properties suggest that this scale can be applied to help understand outcomes after ACLR [42].

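### Recruiting 48 covers at most 16.7% dropout, not the stated 20%, if 40 completers are required

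*Protocol article*

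**What the plan says.** Protocol article, Sample Size Estimation and Study Population: the power calculation gives "a sample size of 20 participants per group (40 participants in total", described as "required to achieve 80% power to detect a large between-group effect in injury-related fear". Its inputs are "a repeated measures ANOVA with a common SD of 1", "a 2-sided α level of 0.05" and "an estimated partial η^2^ of 0.23". The section then concludes that "a total of 48 participants (24 in each group) will be recruited to account for a 20% dropout rate in the sample", and that this number suits both aims.

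Limitations and Anticipated Problems: after noting that the 26 visits may lead to dropout and missing data, the article answers that "our sample size was calculated to account for possible attrition".

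Retention is also a feasibility outcome. Feasibility (Aim 1) states "We expect that more than 75% of participants will be retained during the 8-week period", for both groups. Statistical Analysis sets the minimum acceptable retention at 75%, with exactly 75% counted as acceptable.

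**The concern.** A dropout rate applies to the people recruited, so the required number of completers must be divided by the proportion expected to stay. The plan appears instead to have added 20% of the required 40. Its own dropout assumption then leads to fewer completers than its own requirement, and the reassurance about attrition in the limitations section depends on that step. At stake is whether the stated allowance can be relied on when the Aim 2 results are read after dropout at the planned rate.

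**Working it through.** **Inputs.** Required completers 40 (20 per group), recruitment 48 (24 per group), dropout 20%, partial η² 0.23 and two-sided α 0.05, all from Sample Size Estimation and Study Population. The retention threshold of 75% is from Statistical Analysis.

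**Step 1: reproduce the plan's figure.**
- 40 × (1 + 0.20) = 48; per group 20 × 1.20 = 24. This matches exactly.

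**Step 2: the inflation that the stated dropout needs.**
- 40 / (1 − 0.20) = 50; per group 20 / 0.80 = 25.
- Shortfall: 50 − 48 = 2 participants, one per group.

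**Step 3: what 48 delivers.**
- At 20% dropout: 48 × 0.80 = 38.4 completers; per group 24 × 0.80 = 19.2.
- Largest dropout that still leaves 40: 1 − 40/48 = 16.7%, or 4 of 24 per group.
- Retention needed to keep 40: 40/48 = 83.3%.
- At exactly 75% retention: 48 × 0.75 = 36, or 18 per group.

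**Step 4: effect on power, under two readings of the 40.**

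*(a) Take the plan's word that 20 per group gives 80%.* For a two-sample noncentral t (df = 2n − 2, noncentrality d × √(n/2), α 0.05), this corresponds to d = 0.909. That value is back-solved and stands nowhere in the article.

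*(b) Take partial η² = 0.23 literally.* Then f² = 0.23/0.77 = 0.299 and f = 0.547. Use the noncentral F with 1 and N − 2 df and λ = N × f².

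| Completers | (a) 80% at 40 assumed | (b) η² 0.23, α 0.05 |
|---|---|---|
| 40 (20 per group) | 80.0% | 92.0% |
| 38 (19 per group) | 77.8% | 90.6% |
| 36 (18 per group) | 75.5% | 89.0% |

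Under (b), 80% power is reached at 30 in total, so the stated 40 does not follow from the stated inputs. Two other routes do lead to 40:
- Entering 0.23 as Cohen's f with a pre–post correlation of 0.5 (my assumption; the article gives none), at α 0.05: 80.9%, 78.8% and 76.5% at 40, 38 and 36 completers.
- The literal η² at α 0.05/3, the corrected level in Statistical Analysis: 82.4%, 79.9% and 77.2%.

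The article does not say which route, if any, was used. Across all four, going from 40 to 38 completers costs about 1 to 3 percentage points.

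**The case against.** The strongest reply is that the error is trivial: two participants in a stage 1 feasibility trial whose Aim 1 needs only 24, and which disclaims firm conclusions on effectiveness. That stands as to size. It does not make the stated 20% allowance correct, and nothing elsewhere in the article corrects it.

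Three stronger readings are tempting, and the article does not support them.

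- *That the trial loses its 80% power at 20% dropout.* A reader might infer this from the shortfall against 40. It follows only if 40 gives exactly 80%. On the stated η² and α, power is still about 91% at 38 completers and 89% at 36. What is shown is a missed count, not a lost power target. Lower figures at α 0.05/3 would bring in a separate question, the difference between the planning and analysis significance levels, which has nothing to do with dropout.
- *That the 75% retention threshold contradicts Aim 2.* The threshold judges feasibility; it is not a planning assumption for power. A trial may be feasible to run and still end somewhat below its target size. Moreover, 36 completers passes only under the Statistical Analysis wording. Feasibility (Aim 1) expects retention above 75% in both groups, which means at least 19 of 24 in each.
- *That early dropout already shows the allowance is used up.* Results reports 2 withdrawals among 12 randomized, which is 16.7%. The exact 95% interval is about 2% to 48%, and 16.7% of 48 would leave exactly 40.

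**Conclusion.** The stated dropout allowance is wrong by the plan's own numbers. With 40 completers required, 48 recruited covers at most 16.7% dropout (4 per group). At 20% it leaves about 38, or 19 per group. This needs no assumption beyond the stated 40, 48 and 20%, with dropout counted as a share of those recruited. The statement on attrition in the limitations section carries the same error.

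The severity is minor. If the plan's 80% at 40 is accepted, power falls to about 78%, but that figure is conditional, because the 40 does not reproduce from partial η² 0.23 at α 0.05. The retention threshold is a separate criterion, and its difference from 83.3% is worth a note rather than being an error.

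**What to change.** - In Sample Size Estimation and Study Population, keep 48 and restate the allowance as up to 16.7% dropout (4 per group). Alternatively, keep the 20% assumption and state that about 38 completers (19 per group) are expected.
- Bring the attrition sentence in Limitations and Anticipated Problems into line with whichever is chosen.
- Before quoting power at 19 or 18 completers per group, state how the 40 was obtained from the effect size, significance level and any assumed correlation.
- Optionally, add beside the 75% threshold in Statistical Analysis that it is a feasibility criterion, and that keeping 40 completers for Aim 2 takes 83.3% retention.

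The cost is wording only, with no added participants and no design change. The one downside is a slightly less favourable stated dropout allowance. Raising recruitment to 50 would also repair the arithmetic, but a gap of two does not call for it while the basis of the 40 is unsettled.

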### Recruitment and Eligibility

We will recruit from the student body at the University of North Carolina at Chapel Hill (UNC-CH), the UNC-CH Sports Medicine Institute, and through local community physical therapy clinic partners. All participants will review and sign a university-approved institutional review board informed assent/consent.

### Inclusion Criteria

Participants will be included based on the following inclusion criteria: (1) female sex assigned at birth, (2) age 14 to 35 years old, (3) 6 months to 10 years post ACLR, (4) ACL injury mechanism during sport activity (recreational or organized), (5) self-reported elevated injury-related fear defined as a score ≥17 on the 11-Item Tampa Scale of Kinesiophobia-11 [36] (TSK-11), (6) poor jump-landing movement quality defined as a score ≥5 on the Landing Error Scoring System-Real Time, and (7) cleared to return to unrestricted activity.

Females were selected for this study as female athletes are known to have higher sport dropout rates in adolescence, to be at a greater risk of primary ACL injury, to return to sport at lower rates following ACL injury for a multitude of reasons, and to exhibit differences in injury-related fear [31,37].

